## Abstract

**Background:**

Human adipose-derived Mesenchymal stem cells (HADMSCs) have proven their efficacy in treating osteoarthritis (OA), in earlier preclinical and clinical studies. As the tissue repairers are under the control of mechanical and biochemical signals, improving regeneration outcomes using such signals has of late been the focus of attention. Among mechanical stimuli, low-intensity pulsed ultrasound (LIPUS) has recently shown promise both in vitro and in vivo. This study will investigate the potential of LIPUS in enhancing the regeneration process of an osteoarthritic knee joint.

**Methods:**

This study involves a prospective, randomized, placebo-controlled, and single-blind trial based on the SPIRIT guidelines, and aims to recruit 96 patients initially diagnosed with knee osteoarthritis, following American College of Rheumatology criteria. Patients will be randomized in a 1:1:1 ratio to receive Intraarticular HADMSCs injection with LIPUS, Intraarticular HADMSCs injection with shame LIPUS, or Normal saline with LIPUS. The primary outcome is Western Ontario and McMaster Universities Index of OA (WOMAC) score, while the secondary outcomes will be other knee structural changes, and lower limb muscle strength such as the knee cartilage thickness measured by MRI. Blinded assessments will be performed at baseline (1 month prior to treatment), 1 month, 3 months, and 6 months following the interventions.

**Discussion:**

This trial will be the first clinical study to comprehensively investigate the safety and efficacy of LIPUS on stem cell therapy in OA patients. The results may provide evidence of the effectiveness of LIPUS in improving stem cell therapy and deliver valuable information for the design of subsequent trials.

**Trial registration:**

This study had been prospectively registered with the Chinese Clinical Trials Registry. registration number: ChiCTR1900025907 at September 14, 2019.

## Background

Osteoarthritis (OA) is one of the most significant causes of disabilities among people worldwide. OA affects more than 50 million adults in the United States yearly, resulting in a US$100 billion burden on the economy [1–3]. Current conventional therapies, including physiotherapy agents, pharmacologic interventions, and injections, aim to control pain and improve function; however, they remain unsatisfactory [4, 5]. Likewise, invasive procedures, such as arthroplasty, also have limitations [6, 7].

On the other hand, intra-articular injection of mesenchymal stem cells showed promising results in improving the quality of life and prognosis of OA patients [8–10]. This is because the stem cells are able to migrate and attach to the damaged tissues, actively participate in the regeneration of articular cartilages, and reduce the concentration of prostaglandin in the synovial fluid [11–14].

The environment surrounding the cells can significantly affect tissue repair type and quality. Mechanical stimulation plays a key role in enhancing cell proliferation and differentiation [15, 16]. Several biophysical stimulation agents, including but not limited to electromagnetic fields, electric stimulation, and low-intensity ultrasounds, have exhibited promising effects in promoting stem cell proliferation and differentiation [17–20].

Among the available mechanical stimulation tools, the use of LIPUS in regenerative applications has increased sharply in recent years. LIPUS is presently applied in a variety of biomedical applications, such as physiotherapy, drug and gene delivery, bone fracture healing, and tissue repair [21–23]. Moreover, LIPUS is highly useful, because it is noninvasive, safe, and cost-effective.

Earlier studies presented LIPUS irradiation’s effectiveness in promoting osteogenesis and chondrogenic, inducing the differentiation of MSC, and improving cartilage repair in both in vivo and in vitro studies, which summarize in Table 1 [24–30].

**Table 1 Tab1:** in vitro and in vivo studies of the LIPUS effect on stem cells

First author /Year	Model	Conclusions	Ref.
Ikeda /2006	In Vitro	LIPUS stimulation converts the differentiation pathway of C2C12 cells into the osteoblast and/or chondroblast lineage.	24
Schumann/2006	In vitro	LIPUS could improve in vitro preparation of optimized tissue engineering implants for cartilage repair.	25
Cook /2008	canine	LIPUS improved interface cartilage repair of autologous osteochondral plugs.	26
S.R.Angle /2011	Rat	Ultrasound have a positive effect on osteogenic differentiation of rat bone marrow stromal cells.	27
Ji Hao Cui/2007	Mouse	Ultrasound could be an effective cue to upregulate chondrogenic differentiation of MSCs .	28
Jiang, T /2012	In vitro	LIPUS may induce the osteogenic differentiation of ADSCs in vitro.	29
Jang /2014	In vitro	LIPUS might be used to promote cartilage healing by inducing the migration of CPCs to injured sites.	30
Yamaguchi /2016	Rat	MSC injection with LIPUS is more effective than either treatment in promoting concurrent cartilage repair .	32

*MSC* Mesenchymal stem cells, *ADSC* Adipose stem cells, *CPC* Chondrogenic progenitor cell

Zhou et al. demonstrated that, in addition to accelerating and augmenting the osteogenic differentiation of stem cells, the combination of LIPUS and MSC implantation could prolong the preservation of MSC in vitro [31]. Likewise, Yamaguchi et al. revealed that the combination of the intra-articular injection of MSC and LIPUS showed better results in improving cartilage repair and subchondral reformation in vivo than single treatment [32].

In the present study design, we developed a randomized controlled trial to evaluate the MSC and LIPUS combination among patients with knee osteoarthritis. We hypothesized that the combination of HADMSCs and LIPUS would promote the effectiveness of MSCs in knee cartilage regeneration more than a single-treatment approach.

## Methods

### Study design

This is a randomized, placebo-controlled, single-blinded study protocol, designed following the SPIRIT 2013 statement [33]. A summary of the trial is presented in Fig. 1. Patients will be recruited from the Tongji University Hospital (Huazhong University of Science and Technology, Wuhan, China) orthopedic and rehabilitation departments. Study participation will be promoted through the WeChat mobile application, media reports, and advertisements. Participants will undergo preliminary screenings according to the eligibility criteria. Eligible participants will be invited to take the baseline assessment to confirm that they meet the inclusion criteria and provide written informed consent to participate.The current study was approved by the Tongji Hospital ethics committee (TJ-IRB20180901) and prospectively registered with the Chinese Clinical Trials Registry (ChiCTR1900025907). Written informed consent will be obtained before the patients’ enrollment. Evaluators and data collectors will be blinded as to the groups and treatment allocation.

**Fig. 1 Fig1:**
[figure not shown]
Study flowchart

Treatment groups will receive different treatment regimens as follows:
❖ Group 1: Single intra-articular injection of 10* 10^6^ HADMSCs with low-intensity pulsed ultrasound treatment for 20 min daily, 5 days a week, for up to 8 weeks.❖ Group 2: Single intra-articular injection of 10* 10^6^ HADMSCs with shame ultrasound irradiation for 20 min daily, 5 days a week, for up to 8 weeks.❖ Group 3: Normal saline with low-intensity pulsed ultrasound treatment for 20 min daily, 5 days a week, for up to 8 weeks.

### Inclusion criteria

Males and females aged 18 to 70 Years old.Radiological diagnosis of osteoarthritis using the American College of Rheumatology criteria.Radiological grading of Grade II–III osteoarthritis (OA) of the knee as determined by a qualified radiologist using the Kellgren and Lawrence system.Medial or lateral compartment OA .Less than 5 degrees varus or valgus knee deformity as measured by the long mechanical axis of the knee on x-ray.A minimum pain score of equal or greater than 5/10 on a visual analogue scale (VAS)

### Exclusion criteria

Previous meniscectomy/significant partial meniscectomy or other knee-related surgery within the last 12 months.Previous intra-articular injectable therapies within the last 6 months.The patients who have meniscus injury of knee joint need surgical repair.The patients who have severe coagulation disorders or cardiopulmonary conditions.The women who are pregnant or nursing.There are electronic implants such as pacemakers in the body.The patients who are infected the HIV, the virus of hepatitis or syphilis or Bleeding disorders.The patients with severe cognitive impairment who cannot follow instructions to complete the treatment.History of cancer.Immunodeficiency patients.History of systemic illness or significant organ impairment/failure (i.e., renal failure).The patients who have congenital or acquired knee malformation.Patients or researchers who are participating in other clinical trials believe that other reasons are not appropriate for clinical trials.

### Randomization

Participants will be randomly allocated to one of the three groups in a ratio of 1:1:1. Patients’ allocations will be according to a randomly generated number using a computerized randomization table (http://www.randomization.com). This table of randomization numbers will be provided only to specified personnel at the stem cell center. Moreover, using identical placebo procedures will ensure blinding and a central automated allocation procedure.

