### Sample size calculation

The current study was designed to achieve 80% power overall to detect a 10-point change on the WOMAC between groups after 6 months (the significance level was set at 0.05). Based on an earlier study using a similar outcome measuring method with adding around 20% for the overall attrition rate. Thus a sample size of 96 (32 per group) will be used for estimating a two-sided 95% confidence interval (CI) [48].

The statistical hypotheses are:

H0: mean WOMAC Index (with LIPUS) = mean WOMAC Index (conventional).

HA: mean WOMAC Index (with LIPUS) ≠ mean WOMAC Index (conventional).

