### Statistical analyses

Data will be recorded in the case report form. The outcomes will be presented as the mean ± standard deviation (SD). Data analysis will be done using the SPSS version 24.0 statistical software. Comparing the outcomes between groups will be calculated using analysis of variance (ANOVA) or an alternative nonparametric test if the conditions for parametric tests are not applicable.

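### Kellgren-Lawrence grade is known before allocation, but neither the described allocation nor the stated ANOVA uses it: a modest, avoidable loss of precision with no correction for chance imbalance in severity

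*Protocol article*

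**What the plan says.** - **Allocation** (Protocol article, Randomization): patients are "randomly allocated to one of the three groups in a ratio of 1:1:1", and allocations "will be according to a randomly generated number using a computerized randomization table". The section names the list generator, says who holds the list and mentions a central automated procedure. It names no stratification factor, block or minimisation, and does not say that none is used.
- **Severity at entry** (Inclusion criteria): knees must be "Grade II–III osteoarthritis (OA) of the knee as determined by a qualified radiologist using the Kellgren and Lawrence system". The grade is therefore on file before allocation.
- **Analysis** (Statistical analyses): "Comparing the outcomes between groups will be calculated using analysis of variance (ANOVA"), or a nonparametric alternative. No covariate is named.
- **Size** (Sample size calculation): the study is "designed to achieve 80% power overall to detect a 10-point change on the WOMAC between groups after 6 months", and "a sample size of 96 (32 per group) will be used". About 20% was added for attrition. No SD is given.
- **Outcomes**: WOMAC is primary. Cartilage thickness is secondary, and the MRI section adds cartilage volume and a defect grade. Baseline assessments are planned (Outcome assessments).

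**The concern.** The trial mixes two structural grades in arms of 32 and, as described, uses the grade neither to balance the arms nor to adjust the comparison. If grade predicts outcome, two things follow. The variation between grades stays in the error term and costs power. And if the arms happen to differ in their share of grade III knees, the estimated contrast in this one trial is displaced and the stated analysis does nothing about it. The MRI outcomes are the most exposed in principle, because the hypothesis in the Background concerns cartilage regeneration and K-L grade is the structural grade recorded at entry.

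**Working it through.** **Inputs from the article.** 32 per arm; difference 10 WOMAC points; alpha 0.05, taken as two-sided; power 80%; attrition about 20%, so 32 × 0.8 = 25.6, about 26 completers per arm.

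**Assumptions, because the article gives no figure.** K-L III share p = 0.3, 0.5 or 0.7; WOMAC difference between grades g = 5 to 10 points; SD back-solved below.

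**1. The plan's 96.** It cannot be reproduced independently without an SD. Working backwards with n = 2 × [SD × (1.960 + 0.842) / 10]²:
- SD 12.5 gives 24.5, so 25 per arm; 25 / 0.8 = 31.25, so 32.
- SD 12.8 gives 25.7, so 26 per arm; 26 × 1.2 = 31.2, so 32.

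Thus 3 × 32 = 96 fits one pairwise contrast with an SD of about 12.5-12.8. The power step below uses 12.6, the SD at which a two-sample t test with 26 per arm has 80% power.

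**2. Chance imbalance in grade.** The SD of the difference in K-L III share between two arms is √[2p(1−p)/32]: 11.5 percentage points at p = 0.3 or 0.7, and 12.5 at p = 0.5. With Binomial(32, p) in each arm, the chance that Group 1 differs from Group 2 or from Group 3 (the two contrasts behind the hypothesis) is:

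| Gap in K-L III share | p = 0.3 or 0.7 | p = 0.5 |
|---|---|---|
| 15 points or more | 36% | 42% |
| 20 points or more | 13% | 18% |
| 25 points or more | 7% | 11% |

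For a single pair, a gap of 20 points or more has a chance of 8-10%; for any of the three pairs, 18-23%.

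**3. Effect of a gap on WOMAC.** Shift = gap × g. A 20-point gap gives 0.20 × 5 = 1.0 to 0.20 × 10 = 2.0 points. A 25-point gap gives 1.25 to 2.5 points. The target is 10.

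**4. Power recovered by using grade.** At p = 0.5 grade contributes 0.25 × g² to the variance, so the residual SD is √(12.6² − 0.25g²). Power is for a two-sample t test with 26 per arm and a difference of 10:

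| g | Variance explained | Residual SD | Pairwise power |
|---|---|---|---|
| 0 (grade unused) | 0% | 12.60 | 80.1% |
| 5 | 6.25/158.76 = 4% | 12.35 | 81.7% |
| 8 | 16/158.76 = 10% | 11.95 | 84.1% |
| 10 | 25/158.76 = 16% | 11.57 | 86.4% |

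A normal approximation with SD 12.74 gives much the same: 80.8%, rising to 82.3% (g = 5) and 86.8% (g = 10).

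**5. Type I error of the stated ANOVA.** Simulating 20,000 trials with no treatment effect, g = 10, p = 0.5 and 26 per arm gave 5.2% (simulation error about 0.15 points), which is nominal.

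**6. MRI.** The article gives no variability and no relation to grade for these outcomes, so no size can be calculated.

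**The case against.** The best reply is that nothing here is an error. Randomisation without strata is valid, chance imbalance is already part of the ANOVA error, and step 5 confirms nominal type I error. That stands; the point is about precision and about the particular randomisation that this trial will realise.

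Second, a condensed article may leave blocks and strata to the full protocol, and covariates to the analysis plan. That also stands, so the allocation part is conditional. A reader might infer that the list is a plain one that disregards grade, or that it cannot deliver 32 per arm. The documents support neither reading: the Randomization section is silent on blocks and strata, and a 1:1:1 ratio with 32 per group fits a blocked list at least as well as an unrestricted one. The analysis part is firmer, because the article does state a method, and that method carries no baseline term.

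Third, the size rests on an assumed grade mix, an assumed grade effect and a back-solved SD. True; the ranges are shown for that reason. Eligibility also narrows severity to two adjacent grades, with deformity under 5 degrees and a minimum pain score, so the grade effect could be near the low end or below it.

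Fourth, the article does not say whether follow-up values or changes from baseline are compared. Analysing change would remove part of a starting difference, so an uncorrected effect on MRI is possible but not established.

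**Conclusion.** The point holds as a moderate design improvement. As described, a severity marker recorded for every patient before allocation is used in neither the design nor the analysis. Under the assumptions above, the cost is about 1.5 to 6 points of pairwise power on WOMAC, and a 13-18% chance that at least one key contrast carries a K-L III gap of 20 points or more, worth 1-2 of the planned 10 points.

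Two stronger readings should be resisted. A sizeable imbalance is not more likely than not: even the 15-point threshold is reached in only 36-42% of randomisations. Nor does an imbalance make the test invalid, so it would be wrong to say that it will be mistaken for a treatment effect more often than the nominal 5% allows.

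**What to change.** **Analysis (main change).** In Statistical analyses, replace the group-only ANOVA for WOMAC and the MRI outcomes with a model containing treatment group, K-L grade (II or III) as a fixed factor, and the baseline value of the outcome. Use an ordinal form of the same model for the cartilage defect grade. Both covariates are already collected, so this needs no extra patients, visits or procedures. The power gain in the working is for grade alone; the gain from the baseline value cannot be computed from the article.

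**Allocation (only if not already done).** In Randomization, state whether the list is blocked and stratified. If it is not stratified, prepare it within two strata, K-L II and K-L III, with varied block sizes that are not disclosed to treating staff. This must be settled before the first allocation; a later analysis plan can add adjustment but cannot restore balance.

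**Cost.** A second list, and the grade supplied with each allocation request. Incomplete blocks leave the arms slightly unequal: an unfinished block of six can leave two arms two apart in each stratum, so up to four apart overall. Small blocks at one hospital, with one unblinded therapist treating everyone, would make later assignments easier to guess, which is why sizes should vary and stay undisclosed.

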### Blinding

Blinding both participants and healthcare professionals is not feasible in this type of intervention. However, in order to minimize bias, the outcome evaluation will be standardized and done by well-trained investigators. Furthermore, the investigators and evaluators will be blinded to the group/treatment assignment. After completing the study, the statistician will present un-blinded data to the investigators.

### Autologous HADMSC preparation

For this study, the researcher chose human adipose stem cells as the stem cell source. This is because human adipose stem cells can be easily isolated by a minor invasive approach and in larger quantities than bone marrow. Moreover, human adipose stem cells have a chondrogenic differentiation potential [34–36] In this study, all participants will undergo a lateral abdominal approach to abdominal liposuction harvesting. The participants will be given antibiotics as a prophylaxis course 1 day before and 4 days after the liposuction [37].

The procedure includes anesthesia of the lateral abdominal area. The anesthesia solution contains a tumescent fluid that comprises approximately 30–40 ml of (2%) lignocaine and 1 ml of 1/1000 adrenaline. The mixture will be buffered by 1 ml of 8.4% bicarbonate and then suspended in saline solution to a total of 1000 ml.

Up to 60 ml of adipose tissue and tumescent fluid will be exuded using a 4 mm lipo-aspiration canula. The aspirated subject will be placed in a sterile medical grade Shippert TissuTrans Collection filter (Shippert Medical, CO, USA). A certified and well-trained doctor will conduct the liposuction procedure and all participants will be checked after 1 week of cell harvest.

### Mesenchymal stem cells (MSCs) derivation

we will conduct the isolation and expansion procedure by following the method designed by Zuk et al. [38] The aspirated content in the filter will be treated in a fully sterile environment in a Biological Safety Cabinet (Class II) and obeying strict aseptic systems with (ISO 5) air quality at least. Moreover, all the equipment, reagents, and buffer will be sterile, validated, and qualified for cell culture use. Stromal vascular fraction (SVF) will be isolated by enzymatic digestion followed by centrifugation.

Later, cell culturing will be accomplished under hypoxic conditions and using a standard growth medium (10% fetal bovine serum). The cells will be cultured to reach a confluency of about 80% and later passage 2 (P2). Upon reaching P2, the researcher will wash the cells to remove the fetal bovine serum. Then, HADMSCs will be suspended in a clinical-grade MSC cryoprotectant media and cryo-preserved by a clinical-grade cryoprotectant media [39, 40].

The cells will be detected via flow cytometry (FACS), which will be completed independently on all HADMSC samples using the four surface markers for the MSCs, as indicated by the International Society for Cellular Therapy (ISCT) [41]. The researcher will also test the presence of MSC markers (CD44, CD 90, CD105, and CD 73) and the absence of hematopoietic surface markers (CD 34 and CD45). In addition, all HADMSC samples will undergo independent sterility testing for microbial growth or/and contamination.

Dosages including roughly 10* 10^6^ MSCs each will be frozen separately in sterile cryovials in an approved cell cryoprotectant medium using a validated control rate freezing method and kept in liquid nitrogen until needed [40]. On the day of injection, one cryovial will be liquefied at 37 °C using a sterile water bath and then centrifuged to eliminate the cryoprotectant medium and add injectable sterile isotonic (0.9%) normal saline to a total of 3 ml. Cell count and viability will be established through the use of a Muse Cell Analyzer (Merck Millipore, USA).

### Interventions

#### HADMSC intra-articular injection technique

At the time of injection, the patient’s knee will be prepared following the standard sterile procedures. To ensure the accurate intra-articular placement of the needle, the injection will be carried out under continuous ultrasound guidance.

A total of 2 ml of (1%) lidocaine will be injected subcutaneously to reach the knee joint capsule and provide local anesthesia under aseptic settings. Then, roughly 10 million HDAMSCs will be injected into the intra-articular area using the superolateral patella approach. Patients in the sham injection treatment group will be injected an equivalent volume of sterile saline at the same interval of stem cells treatment group.

#### Ultrasound therapy

In the LIPUS treatment patients, LIPUS will be applied using an aqueous gel that does not include any pharmacological substances as a conduction medium. LIPUS will be applied in circular movements with the applicator probe at right angles to achieve maximum absorption of the energy. The treatment areas will include both the tibiofemoral and patellofemoral borders of the target knee on both the medial and lateral margins, making sure to avoid to patella.

Pulsed ultrasonic waves of (1 MHz) frequency and 0.5 w/cm2 intensity will be applied with a 5 cm diameter applicator probe for 20 min (Sonopuls 590, EnrafNonius BV, The Netherlands). On the other hand, patients in the placebo ultrasound treatment will receive the same number of treatment sessions of a similar duration as those in the experimental group. While the sham LIPUS treatment will only use inactive doses of LIPUS with an intensity of 0 W/cm2, along with the gentle application of an inert-gel for 20 min to the treated area [42, 43]. The placebo treatment protocol has been successfully examined in previous studies [44, 45].

Patients recruited to LIPUS will have the treatment once a day, 5 days a week for 8 weeks. All patients will be treated by the same therapist, who was not blinded to the treatment groups as the therapist will set the setting parameters.

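### The therapist is unblinded to the treatment groups although setting the device needs only active or sham, and the randomization table is not reconciled with the claimed central allocation

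*Protocol article*

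**What the plan says.** **Therapist.** In the protocol article, Ultrasound therapy, all patients are treated by "the same therapist, who was not blinded to the treatment groups as the therapist will set the setting parameters". Setting the device is the only reason offered.

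**Device settings, same section.** Active: "Pulsed ultrasonic waves of (1 MHz) frequency and 0.5 w/cm2 intensity will be applied". Sham: "the sham LIPUS treatment will only use inactive doses of LIPUS with an intensity of 0 W/cm2".

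**Arms, in the list under Study design.** "Group 1: Single intra-articular injection of 10* 10^6^ HADMSCs with low-intensity pulsed ultrasound treatment"; Group 2 receives "HADMSCs with shame ultrasound irradiation for 20 min daily, 5 days a week, for up to 8 weeks"; Group 3 receives saline with active LIPUS. The list introduces these three arms as the treatment groups, the term the therapist sentence uses.

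**Randomization.** "This table of randomization numbers will be provided only to specified personnel at the stem cell center". The next sentence states that "using identical placebo procedures will ensure blinding and a central automated allocation procedure". The automated procedure is not described further.

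**Blinding.** The section says it is not feasible to blind both participants and health professionals, and that investigators and evaluators are blinded.

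**The concern.** The trial's hypothesis, in the Background and again in the Discussion, is that cells plus LIPUS do better than either alone. That rests on two contrasts: Group 1 against Group 2 (the LIPUS contribution) and Group 1 against Group 3 (the cell contribution). For the second, the protocol has already provided the means of masking: all participants undergo liposuction, and the sham injection is saline of equal volume.

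One therapist then sees each patient up to 40 times. If that person knows who received cells, expectation can pass to the patient through manner or remarks. Blinded evaluators do not close this route, because a WOMAC score reflects what the patient reports. Where the therapist has no use for the information, the exposure buys nothing.

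The allocation list raises a related question of who needs to know what. To prepare an injection, the center needs cells or saline for the patient in hand. The article gives no reason for it to hold LIPUS status or future assignments, which a full table would show.

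**Working it through.** The point depends on no figure stated in the plan, so there is none to reproduce. The check is what each level of knowledge reveals.

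**Inputs.** 96 patients, 32 per group (Sample size calculation); 1:1:1 allocation (Randomization); five 20-minute sessions a week for 8 weeks (Ultrasound therapy), with the arm list giving 8 weeks as an upper limit; device settings and arms as quoted.

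**Step 1: map arms to what has to be known.**

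| Group | Injection | Device | Patients |
|---|---|---|---|
| 1 | cells | active, 0.5 W/cm2 | 32 |
| 2 | cells | sham, 0 W/cm2 | 32 |
| 3 | saline | active, 0.5 W/cm2 | 32 |

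The therapist's task depends on the device column only. Groups 1 and 3 have the same setting.

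**Step 2: chance that the therapist can name a patient's arm, with no other information.**

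- Told nothing: 1/3.
- Told active or sham: (1/3 × 1) + (2/3 × 1/2) = 2/3. Sham identifies Group 2; active leaves Groups 1 and 3 undetermined.
- Told the group: 1.

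**Step 3: who is affected.** For the 32 sham patients, group knowledge adds nothing to knowing sham. For the other 32 + 32 = 64 it adds cells or saline.

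**Step 4: contact.** 5 × 8 = 40 sessions per patient at most. Avoidable exposure: 64 × 40 = 2,560 sessions at most, or 2,560 × 20 / 60 ≈ 853 hours. The remaining 32 × 40 = 1,280 sessions are in Group 2 and would be unaffected by any change.

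**Step 5: the stem cell center.** The structure is symmetric. Told only cells or saline, staff can identify Group 3 (the only saline arm) but not separate Group 1 from Group 2: (1/3 × 1) + (2/3 × 1/2) = 2/3. A full table raises this to 1 and also shows assignments not yet made.

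**Step 6: the two Randomization sentences side by side.** One puts the table with named-role staff at the center. The other attributes a central automated procedure to identical placebo procedures, but the latter can support blinding and cannot produce an allocation mechanism. The text does not say which of the two releases an assignment.

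**The case against.** **Treatment groups may be meant narrowly.** The sentence stands in the ultrasound section, which speaks of LIPUS against sham, and is justified by the settings. On that reading the therapist already knows only active or sham. This is a fair reading and the text does not exclude it. But the arm list uses the same term for the three arms, so the literal reading is the wider one, and the sentence needs changing under either.

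**Masking may leak.** The Blinding section concedes that participants and professionals cannot both be blinded. A patient who knows the injection can tell the therapist at any session, and that patient's WOMAC is then exposed directly. This stands: the change reduces exposure and does not guarantee masking. It also does nothing for Group 1 against Group 2, which may be what the hypotheses under Sample size calculation (LIPUS against conventional) refer to.

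**A reader might infer that concealment is broken.** The documents do not show it. The table is restricted to specified personnel; nothing says they enrol patients, and recruitment runs through the orthopedic and rehabilitation departments. The center could itself be the central holder. What remains is an unreconciled description.

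**A reader might count all 96 × 40 = 3,840 sessions.** That includes Group 2, where disclosure is unavoidable.

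**A reader might hold back each allocation until the patient's cell batch is released.** Nothing says Group 3 cells are cultured. That rule could therefore mean expansion, testing and freezing for 32 saline patients, which is not a small change and is not needed here.

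**Conclusion.** The point holds in a limited form. On the literal reading, the plan tells the therapist more than the stated reason requires: cells or saline for 64 of 96 patients, over at most 2,560 sessions, bearing on the Group 1 against Group 3 contrast. This assumes that treatment groups means the three listed arms and that all sessions are delivered. If the narrower meaning is intended, the defect is one of wording only.

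No bias in WOMAC points and no inflated false-positive rate can be attached to this. Either would need an assumed bias and a standard deviation, and the article gives neither. The argument for the change is that the disclosure serves no purpose and is cheap to remove.

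On the allocation list, the conclusion is that two adjacent sentences must be reconciled. It is not a finding that allocation was or will be foreseen by those who enrol.

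**What to change.** **Ultrasound therapy.** State that the therapist receives only active or sham for each patient and is not told the injection content. No added rule on outcome collection is needed: the article already requires evaluators and data collectors blind to allocation, which excludes an unblinded therapist.

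**Randomization.** State that the central system holds the list and releases one assignment at a time after enrolment, and that the stem cell center is told only cells or saline for the current patient. Separate this from the remark on identical placebo procedures, which concerns blinding.

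**Cost.** A few sentences and a set-up of the allocation messages so that each recipient sees one item. Treatments, sample size, alpha and power are untouched. The limitation to acknowledge is that patients may still reveal what they know, so the therapist's masking to the injection should be described as intended, not assured.
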